**4 Study description**

##

4.1a Study design

*Non-invasive vs Invasive measurements.*

For each patient enrolled into the study, a total of three ICPtcd measurements will be performed in three different time frames, each of which will be compared to the corresponding ICPi for concordance.

- The first ICPtcd measurement (TIME 1) will be performed before ICPi placement (< 30 min.) and will be compared with the first ICPi reading once the probe is positioned. The need to reduce the time gap as much as possible between the two readings is motivated by the fact that ICP may be subjected to variations caused by ABP manipulation, cerebrospinal fluid (CSF) leakage during catheter placement and pharmacological treatment or fluctuations due to the evolving underlying brain injury.

-The second ICPtcd measurement (TIME 2) will be performed immediately after insertion of the ICPi probe and compared with the post-insertion ICPi reading. The ICPi measurement to be confronted with the ICPtcd estimated measurement for concordance must be read simultaneously.

- The third ICPtcd measurement (TIME 3) is performed between 2 and 3 hours following the second reading. The reason for this is to avoid any possible variations in systemic and cerebral hemodynamics caused by the ICPi device insertion itself, despite sedation. Therefore, performing the examination more than 2 hours post insertion should reduce the influence of the positioning maneuver on the readings. The ICPi measurement to be confronted with the ICPtcd estimated measurement for concordance must be read simultaneously.

In accordance with the present guidelines, intracranial hypertension is defined as an ICP above 22 mmHg, which remains so for at least 10 minutes and is not related to procedural pain [16]. Therefore, intracranial hypertension is considered such only when the ICPi reading meets this criteria.

However, when analysis will be performed the ICPtcd may be confronted to three different ICP values for concordance correlation (ICPi=20mmHg, ICPi=22mmHg, ICPi=25mmHg,).

*Patient sedation.*

Patient sedation for ICP bolt placement may consist of either bolus doses of sedatives and or analgesics and when necessary, neuromuscular blockade of choice, as long as these have been administered either before or after, and not between, the first concordance correlation. As mentioned previously this restriction is not necessary for the following two Time frames.

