## 7 Organization

7.1 Collecting data

Data collection will be performed by the personal pertaining to each single center and entered into an on-line data collection program (RedCap), which will automatically be downloaded by the coordinating center for analysis.

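### Sections 4.1a and 9 define disease status differently; under 4.1a an unmasked judgement on procedural pain could enter the reference label.

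*Protocol*

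**What the plan says.** Protocol section 4.1a sets the definition: intracranial hypertension means an ICP of more than 22 mmHg, "which remains so for at least 10 minutes and is not related to procedural pain". It makes this binding: "Therefore, intracranial hypertension is considered such only when the ICPi reading meets this criteria". It adds that, at analysis, ICPtcd may also be compared with ICPi values of 20, 22 and 25 mmHg.

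The same section fixes the order of the tests. The TIME 1 ICPtcd "will be performed before ICPi placement (< 30 min.) and will be compared with the first ICPi reading once the probe is positioned". The TIME 2 ICPtcd "will be performed immediately after insertion of the ICPi probe and compared with the post-insertion ICPi reading", with the two values read at the same moment. TIME 3 comes two to three hours later, and the stated reason "is to avoid any possible variations in systemic and cerebral hemodynamics caused by the ICPi device insertion itself, despite sedation".

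Section 9 gives another rule. ICPi is split at 22 mmHg, and sensitivity and specificity are defined on values above 22 and on values of 22 or below. Neither duration nor pain is mentioned.

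On recording, section 7.1 says: "Data collection will be performed by the personal pertaining to each single center". The protocol nowhere mentions masking of either measurement, and it does not say who decides that a rise is due to pain, when, or by what criteria.

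**The concern.** The primary outcome (section 3.1) is the NPV, PPV, sensitivity and specificity of ICPtcd against invasive ICP, and all four depend on who counts as diseased. Two rules are in force. A brief rise above 22 mmHg, or a sustained one put down to pain, is positive under section 9 and negative under section 4.1a.

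The pain condition also raises a problem of its own, because it is a judgement and not a reading. It falls mainly on the TIME 1 and TIME 2 readings, which follow insertion directly and which the protocol itself expects insertion to disturb. At TIME 1 the Doppler measurement already exists when the first ICPi value appears. ICPtcd is simple arithmetic from MABP and two flow velocities (section 11), so it can be worked out at the bedside.

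If the person judging pain knows that ICPtcd is low, a high ICPi may more readily be put down to pain. That would remove false negatives, the cell on which a claim to exclude hypertension rests.

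**Working it through.** **Inputs.** From section 4.2: 490 patients, prevalence 30%, sensitivity 90%, power 95%, and a lower limit stated as 10%, read here as 10 points below 90%, i.e. 80%. Assumed, because the documents do not give them: a one-sided 5% level, specificity 70% (varied from 50% to 90%), and the number of readings relabelled.

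**The plan's own figure.** The exact binomial method asks for the number of cases from which the chance that the one-sided 95% lower limit reaches 0.80, given a true sensitivity of 0.90, stays at or above 0.95. This gives 147 cases, and 147 / 0.30 = 490. The stated sample size is reproduced.

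**Table before relabelling (whole patients).** Cases: 490 x 0.30 = 147. True positives: 147 x 0.90 ≈ 132. False negatives: 147 - 132 = 15. Non-cases: 490 - 147 = 343. True negatives: 343 x 0.70 ≈ 240. False positives: 343 - 240 = 103.

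**Relabelling driven by ICPtcd.** Move k patients from false negative to true negative:

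- sensitivity = 132 / (147 - k)
- NPV = (240 + k) / 255

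| k | Sensitivity | NPV |
|---|---|---|
| 0 | 132/147 = 89.8% | 240/255 = 94.1% |
| 3 | 132/144 = 91.7% | 243/255 = 95.3% |
| 5 | 132/142 = 93.0% | 245/255 = 96.1% |
| 8 | 132/139 = 95.0% | 248/255 = 97.3% |

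**Dependence on the assumed specificity.** With a quarter of the false negatives relabelled (unrounded counts), NPV rises from 0.921 to 0.941 at specificity 0.50, from 0.942 to 0.957 at 0.70, and from 0.955 to 0.966 at 0.90. Sensitivity goes from 0.900 to 0.923 in each case.

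**Pain judged without regard to ICPtcd.** Relabel 25% of all cases, true positives and false negatives alike. The unrounded starting counts are TP 132.3, FN 14.7, TN 240.1, FP 102.9; 33.075 true positives become false positives and 3.675 false negatives become true negatives.

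- Sensitivity: 99.225 / (99.225 + 11.025) = 0.900, unchanged.
- NPV: 243.775 / 254.8 = 0.957, up from 0.942.
- Specificity: 243.775 / (243.775 + 135.975) = 0.642, down from 0.700.
- PPV: 99.225 / 235.2 = 0.422, down from 0.563.

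**Section 9 rule.** Status depends on ICPi above 22 mmHg alone. No reading can be relabelled for pain, so k = 0 and nothing changes.

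**The case against.** The strongest reply is that section 9, the only statistical section, already uses the plain cut. Section 4.1a itself turns to plain cut-offs when it speaks of analysis. On that reading the pain condition describes clinical hypertension and never reaches the 2x2 table. This may be what was meant, but section 9 does not say that it replaces 4.1a, and 4.1a uses the word only. The conflict stands.

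A reader might infer that staff already know ICPtcd when they judge pain, so that sensitivity and NPV will be inflated. The documents do not support this. Knowledge of ICPtcd is inferred from the test order at TIME 1 and the silence on masking. Section 7.1 does not say that one person records both values, and no text says when ICPtcd is calculated or who sees it. At TIME 2 the values are simultaneous, so only the TIME 1 value could be known beforehand. Nor is the bias bound to favour the test: if pain is judged without regard to ICPtcd, sensitivity does not move and two of the four primary measures get worse.

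Three further limits also stand. The ICPtcd threshold is chosen at analysis by the Youden criterion, so the false-negative cell is not fixed at the bedside. Section 9 also averages measurements over time, and TIME 3 lies largely outside the mechanism; the illustration covers one reading per patient. Finally, the pain condition is attributed to guidelines, and dropping it from the study label counts some procedural rises as disease.

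**Conclusion.** The firm finding is a contradiction: sections 4.1a and 9 give different disease definitions for the primary outcome and must be reconciled. The bias is conditional. It needs 4.1a to govern, and the rise in sensitivity also needs the person assessing pain to know ICPtcd. Under those conditions, relabelling 3 to 8 of about 15 false negatives raises sensitivity by about 2 to 5 points and NPV by about 1 to 3 points. These sizes rest on an assumed specificity of 70% and on relabelling counts for which the documents give no rate. Under section 9 alone the effect is zero.

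The point is still worth settling in the protocol. An analysis plan can choose between the two rules, but it cannot make a bedside judgement masked after the event.

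**What to change.** State one rule for study disease status in the primary analysis, in the same words in sections 4.1a and 9, resting on recorded ICPi values only. Say in both places whether the duration condition is part of it; if it is, it must be derived from recorded values.

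Record procedural pain as a separate yes/no field in REDCap, completed before ICPtcd is calculated or seen. Repeat the analysis without the flagged readings and report it beside the main one.

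The cost is a sentence in each of two sections, one data field and one repeat analysis. The downside is that some transient insertion-related rises will count as positive in the main analysis, so the accuracy figures may be slightly less favourable. The change concerns the study label only and leaves the clinical definition used for patient care as it is.

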# - Middle Cerebral Artery Diastolic Flow Velocity (FVd-mca)

# - Middle Cerebral Artery Mean Flow Velocity (FVm-mca)

During the three time frames measurement of CO_2_  crucial. At time frame 1° both ET CO_2_ and PaCO_2_ can be measured for calibration. However it is suggested to use the same measurement parameter for all three time frames, whether it be ET CO_2_ or PaCO_2_.

# *Throughout the trial all patients will receive standard clinical treatment according to the international guidelines for the treatment of various types of brain injury.

4.2 Sample size

Sample size was estimated using the approach suggested by Flahault et al. (2005) and H. Chu and S.R. Cole (2007), assuming a *true* sensitivity of the test (ICPtcd) of 90%, a prevalence of the disease (intracranial hypertension) equal to 30%, a power of 95% and a lower acceptable confidence limit of 10%.

We calculated an overall sample size of **490** patients

4.3 Expected study duration: at completion of the inclusion of 490 patients, roughly two years are expected to be recruited.

# 5 Study population

# 5.1 Inclusion criteria

# brain injury (Traumatic Brain Injury, Subarachnoid Hemorrhage, Intracerebral hemorrhage, Ischemic stroke);

# patients requiring invasive ICP monitoring (intraparenchymal, post-craniotomy or post-surgical, Intra-ventricular);

# age > 18 yrs.

# 5.2 Exclusion criteria

# - inaccessible or poor acoustic ultrasound window,

# - a cardiovascular disease causing hemodynamic variations affecting the TCD reading (severe arrhythmia, severe cardiac valvular stenosis, moderate or severe vasospasm),

# - Patient already with craniotomy or craniectomy before first time frame 1°,

# - any treatment for intracranial hypertension or manipulation of arterial blood pressure intervening between the non-invasive ICPtcd measurements and the invasive ICP (ICPi) measurement. (This is most likely to happen during time frame 1°). For this reason it is stressed that if the patient requires invasive ICPi monitoring to be performed in the operating room, than the non-invasive ICPtcd measurement should be performed just before the patient leaves the ICU (or if possible the ER) towards the OR for insertion. This would reduce the time during which the patient may be prone to ABP and ICP manipulation.

# 6 Detailed study course

#

Flow diagram

[figure not shown]

## 7 Organization

7.1 Collecting data

Data collection will be performed by the personal pertaining to each single center and entered into an on-line data collection program (RedCap), which will automatically be downloaded by the coordinating center for analysis.

7.2 Data management and archiving

7.2.1 Data property

Property of the data belongs to the coordinating center (Brescia).

7.2.2 Data control

Control of the data will be performed by the coordinating center.

7.2.3 Subsequent use of data

Initial use of the data belongs to the centers pertaining to the coordinating center until the data has been processed and analyzed for the first publication. Further use of the data for subsequent publications may be possible by part of the steering committee.

7.2.4 Archiving

Data will be archived by the coordinating center who will assume responsibility.

7.3 Sponsorship

No sponsorship nor funding.

## 8 Ethics and Consent

## Ethics approval for all participating sites will be obtained from the appropriate regulatory committees. Detailed written information will be provided to the family members regarding the study protocol, the scope of research, and the safety of TCD examination. Since all patients are presumed to have an altered state of consciousness, the ethics committees will waive the requirement for consent, as in Italy relatives are not regarded as legal representatives of the patient in the absence of a formal designation.

##

8.1 Approval by ethics committee: *NP 2762

8.2 Informed consent: Written informed consent will be requested from all surviving patients as soon as they regaine their mental competency.

**9 Statistical analysis**

Receiver operating curve (ROC) and the area under the curve (AUC) will be estimated after measurement averaging over time and as well as using time-dependent ROC. Values of ICPi will be dichotomized using a standard reference value of 22 mmHg. Confidence interval for AUC, sensitivity and specificity will be computed using bootstrapping (B = 10000). The sensitivity is expressed as the probability that a patient with high ICPi (>22 mmHg) would also have a high ICPtcd value, and the specificity as the probability that a patient with normal ICPi (≤22 mmHg) would also have a normal ICPtcd value. Best threshold for marker will be computed using Youden criterion [18–21].

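### Section 9 averages the three readings before the ROC analysis, which conflicts with the pairwise comparison and the per-reading definition of intracranial hypertension in section 4.1a

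*Protocol*

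**What the plan says.** Section 4.1a plans three ICPtcd measurements per patient, "each of which will be compared to the corresponding ICPi for concordance". TIME 1 is scanned less than 30 minutes before the probe is placed and "will be compared with the first ICPi reading once the probe is positioned". TIME 2 follows insertion immediately and TIME 3 comes 2 to 3 hours after TIME 2; both must be read simultaneously with ICPi. The stated reason for TIME 3 is that "performing the examination more than 2 hours post insertion should reduce the influence of the positioning maneuver on the readings". The same section defines intracranial hypertension as ICP above 22 mmHg lasting at least 10 minutes and unrelated to procedural pain, and counts it only when the ICPi reading meets that definition.

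Section 9 takes another route. ROC and AUC "will be estimated after measurement averaging over time and as well as using time-dependent ROC". It continues: "Values of ICPi will be dichotomized using a standard reference value of 22 mmHg". Sensitivity is defined per patient, as "the probability that a patient with high ICPi (>22 mmHg) would also have a high ICPtcd value". It does not say which of the two approaches supplies the primary NPV, PPV, sensitivity and specificity of section 3.1.

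**The concern.** Averaging changes both sides of the comparison.

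- **The test.** The stated purpose is to exclude intracranial hypertension with TCD. Only TIME 1 precedes the probe. The other two scans exist because the probe is already in, so a three-scan mean is not available to anyone deciding whether to place one.
- **The disease label.** A mean of readings more than two hours apart is neither the corresponding ICPi nor a pressure above 22 mmHg sustained for 10 minutes. A patient who was hypertensive at insertion can be classed as normal because of a later reading, and a TCD that missed the hypertension at TIME 1 can then count as a true negative.
- **The weighting.** The TIME 1 and TIME 2 reference readings both sit at insertion, so that moment gets about two thirds of the weight in the mean. Section 4.1a added TIME 3 precisely to get away from it. Section 5.2 excludes treatment or blood-pressure manipulation within a pair, but nothing excludes it between TIME 2 and TIME 3, so the mean can mix different states.

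At stake is what the reported accuracy figures describe.

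**Working it through.** **1. The plan's own figure.** Section 4.2 gives sensitivity 90%, prevalence 30%, power 95% and a limit of 10%, read here as 10 points below 90%, so 80%. The significance level is not stated; one-sided 0.05 reproduces the result. The exact binomial calculation needs 147 hypertensive patients (at least 126 detected; power 96.4%), and 147 / 0.30 = 490. The sample size therefore assumes one test result and one label per patient at 30% prevalence. It is not in error.

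**2. The label, by hand.** ICPi of 30, 18 and 16 gives 64 / 3 = 21.3, which counts as normal despite a reading of 30. If TIME 1 and TIME 2 are equal at x, the mean is at or below 22 when TIME 3 ≤ 66 − 2x. For x = 30, TIME 3 must be 6 or lower; for x = 23.3, it need only be 19.4 or lower. Without a systematic fall, the patients who switch are mostly borderline.

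**3. Inputs for a simulation (400,000 patients).**
- TCD error SD: section 2 says the CPP error is below 10 mmHg in more than 80% of measurements. Under normality, 10 / 1.2816 = 7.80 mmHg. At the same arterial pressure, an error in CPP is an equal error in ICP.
- Assumed, not in the protocol: ICPi SD 8 mmHg; 30% above 22, so the mean is 22 − 8 × 0.524 = 17.8; within-patient ICPi correlation 0.7; TIME 1 and TIME 2 ICPi equal; error correlation varied from 0 to 1; a fall by TIME 3 of 0, 5, 8 or 10 mmHg in patients hypertensive at TIME 1.

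**4. Relabelling (does not depend on TCD error).**

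| Fall by TIME 3 | TIME 1 hypertensives relabelled normal | Prevalence on the mean | Expected cases in 490 |
|---|---|---|---|
| 0 | 14% | 28.6% | 140 |
| 5 | 30% | 23.9% | 117 |
| 8 | 41% | 20.5% | 100 |
| 10 | 48% | 18.4% | 90 |

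If TIME 1 and TIME 2 are instead allowed to differ like any other two readings, with no fall, the relabelled share is 44%, 35%, 25% and 13% at within-patient correlations of 0.3, 0.5, 0.7 and 0.9.

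**5. AUC of the averaged analysis.** TIME 1 alone gives 0.845. Simulation error is about 0.001.

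| Error correlation | No fall | Fall 5 | Fall 8 | Fall 10 |
|---|---|---|---|---|
| 0 | 0.920 | 0.902 | 0.895 | 0.890 |
| 0.3 | 0.888 | 0.869 | 0.859 | 0.854 |
| 0.5 | 0.869 | 0.849 | 0.840 | 0.836 |
| 0.7 | 0.854 | 0.833 | 0.825 | 0.818 |
| 1.0 | 0.834 | 0.813 | 0.804 | 0.799 |

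The averaged AUC lies above or below 0.845 depending on two quantities that the protocol does not give.

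**The case against.** A reader might infer that averaging inflates discrimination. The documents do not support this. The same formula, with its fixed offset of 14 (section 2 and Appendix 11), is applied to the same patient within hours, so much of the error may be shared. As that share rises, the AUC gain shrinks and then reverses. The two harms also pull against each other: the larger the fall by TIME 3, the more relabelling but the smaller any AUC gain. This objection stands.

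Nor is it established that the averaged result is the headline. Averaging is named first, but section 9 ranks nothing, and a second analysis stands beside it. That ICPi is averaged is likewise implied rather than stated. It is the natural reading, since averaging is followed directly by dichotomising ICPi with one status per patient.

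Time-dependent ROC often denotes methods for event times, and none are collected here. But the phrase can also be read as a ROC per time frame, which is what section 4.1a calls for. This is a matter of wording, not proof of a wrong method.

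A serious loss of power might also be inferred. Without a fall, 140 expected cases still give exact power of about 93%. The drop to 88% and 81% (117 and 90 cases) rests on an assumed fall of 5 or 10 mmHg.

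Finally, TIME 1 is not beyond dispute as primary. It is the only pair not read simultaneously, and section 4.1a itself warns that ICP may shift in that gap.

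None of this removes the conflict between sections 4.1a and 9.

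**Conclusion.** The point holds as an internal conflict that decides what the accuracy results mean. Followed as written, and with ICPi averaged as implied, section 9 evaluates a three-scan mean against a mean-pressure label. Section 4.1a specifies single pairs and a sustained reading above 22 mmHg. The relabelling is the firmer consequence, because it does not depend on TCD error: about 14% of TIME 1 hypertensives under the stated assumptions, and 30% to 48% with an assumed fall of 5 to 10 mmHg. These shares depend on an ICPi SD and correlation that the protocol does not supply. The effect on AUC has no fixed direction: without a fall it ranges from 0.92 to 0.83 against 0.845, and it is lower at every error correlation once a fall is assumed. Claims of inflated accuracy or of an underpowered study go beyond the documents. Because two analyses with different labels could each supply the primary figures, the text should be settled before the data are analysed.

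**What to change.** In section 9:

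- Replace averaging as the main estimation method with ROC, sensitivity, specificity, NPV and PPV for each time frame separately, using one unaveraged pair per patient and the section 4.1a label, including the 10-minute condition.
- Name one time frame as primary in advance. TIME 1 matches the use before insertion; if it is chosen, acknowledge that its pair is not simultaneous. Report the other two as secondary.
- Reword time-dependent ROC as time-frame-specific ROC.
- For any estimate pooled over frames, use unaveraged pairs and a bootstrap that resamples patients, not readings.
- Keep an averaged analysis at most as a labelled sensitivity analysis, stating whether ICPi is averaged as well.

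The cost is a rewording of section 9 and a little more analysis. The reported accuracy may turn out less favourable. No new data are needed, and 490 stands because its calculation already assumes one result and one label per patient.

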11.1 Formula’s

**1 General information**

- 1. **Organisation**

| Principle Investigator | - [name]: Neuro Critical Care, Azienda Ospedaliera Spedali Civili di Brescia, University of Brescia, (Italy) |
| --- | --- |
| Steering committee | - [name]: Neuro Critical Care, New York Presbyterian Hospital, Columbia University, New York (USA) - [name]: Neuro Critical Care, Addenbrooke’s NHS trust, Cambridge University, (UK) - [name]: Université Libre de Bruxelles , Hôpital Erasme, Brussels (Belgium) - [name]: Centre Hospitalier Universitaire Grenoble Alpes, Pôle Anesthésie Réanimation - [name]: Neuro Critical Care, Azienda Ospedaliera San Gerardo di Monza, Università degli studi Milano-Bicocca, (Italy) |
| **Coordinating center** | Neuro Critical Care Unit, Department of Anesthesiology, Intensive care, and emergency Medicine, Spedali Civili Hospital of Brescia, University of Brescia, Italy |
| Study Statistician | [name], Statistica medica e biometria, Statistician at the University of Brescia, Italy |
| **Data Management for IMPRESSIT-2 study purposes** | Study coordinators |

- 1. **Protocol summary**

| Title of the study | **Discriminant accuracy of Trans-Cranial Doppler to Exclude Intracranial Hypertension in Brain Injured Patients: The IMPRESSIT-2 Prospective Multicenter International Study** |
| --- | --- |
| **Primary outcome** | The NPV, PPV, sensitivity and specificity of ICPtcd estimation in excluding true intracranial hypertension, as measured by the gold standard invasive monitoring technique (ICPi). |
| **Design** | Prospective, observational, non-interventional, non-randomized, non-profit, international, multicenter, clinical study |

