# Finally, ICP is calculated:

# non-invasive ICP = MAP - non-invasive CPP [Appendix **]

# 3 Study endpoints

##

3.1 Primary outcome: the negative predictive value, positive predictive value, sensitivity and specificity of ICPtcd estimation in excluding true intracranial hypertension, as measured by the gold standard invasive monitoring technique (ICPi) [with catheters inserted either into the brain parenchyma or ventricles].

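### The only rule given for the ICPtcd cut-off is Youden on the study's own data, which does not target the rule-out aim and gives modestly optimistic accuracy

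*Protocol*

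**What the plan says.** The title announces "Discriminant accuracy of Trans-Cranial Doppler to Exclude Intracranial Hypertension in Brain Injured Patients". Section 3.1 makes four measures primary: NPV, PPV, and the "sensitivity and specificity of ICPtcd estimation in excluding true intracranial hypertension". Section 4.2 sizes the study on sensitivity alone. It assumes a true "sensitivity of the test (ICPtcd) of 90" per cent, prevalence 30%, power 95% and a 10% lower limit, and arrives at 490 patients.

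Section 9 is specific about the reference standard: "Values of ICPi will be dichotomized using a standard reference value of 22 mmHg". For the index test it gives no number. Sensitivity is the probability that a patient with raised ICPi "would also have a high ICPtcd value". The only rule for turning ICPtcd into high or normal is "Best threshold for marker will be computed using Youden criterion". The interval method is "Confidence interval for AUC, sensitivity and specificity will be computed using bootstrapping (B = 10000" resamples), without saying whether the cut-off is chosen again in each one.

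The values 20, 22 and 25 mmHg in section 4.1 are set on ICPi, so they do not supply an ICPtcd cut-off. One cohort is described. The protocol mentions neither a validation sample nor a correction for optimism.

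**The concern.** All four primary measures depend on where the ICPtcd cut-off lies, so the rule that places it decides the headline result. Youden maximises sensitivity plus specificity: a one-point loss of sensitivity is traded against a one-point gain in specificity. A test meant to exclude a condition needs the missed-case rate held low first. The sample size reflects that priority, since it rests on sensitivity, but the cut-off rule does not.

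The cut-off would also be chosen and assessed in the same patients. The reported accuracy is then that of the best-looking point in this sample, which is on average better than the same point would perform in new patients.

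**Working it through.** **Reproducing 490.** Read the 10% limit as 10 points below 90%, that is 80%. For an exact one-sided binomial test at 5% of 80% against 90%, the smallest number of cases from which power stays at or above 95% is 147. Success needs at least 126 of 147 detected (exact alpha 0.0475, power 0.964). Then 147/0.30 = 490, an exact match. The calculation refers to a cut-off whose true sensitivity is 90%.

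**Model for the Youden point.** Inputs from the protocol are 490 patients and prevalence 0.30 (147 cases, 343 non-cases). The AUC is an assumption, because the protocol gives none. ICPtcd is taken as normal with equal variance in cases and non-cases, with one value per patient.

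- Separation: d = √2 × Φ⁻¹(AUC)
- Youden point: sensitivity = specificity = Φ(d/2)
- Specificity at 90% sensitivity: Φ(d − 1.2816)
- NPV = 0.7 Sp / [0.7 Sp + 0.3 (1 − Se)]

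Example at AUC 0.85: d = 1.414 × 1.036 = 1.466. The Youden point is Φ(0.733) = 0.768, with NPV = 0.5376/(0.5376 + 0.0696) = 0.885. At 90% sensitivity, specificity is Φ(0.184) = 0.573 and NPV = 0.4011/(0.4011 + 0.0300) = 0.930.

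| AUC (assumed) | Youden Se = Sp | Youden NPV | Sp at Se 90% | NPV at Se 90% |
|---|---|---|---|---|
| 0.80 | 0.724 | 0.860 | 0.464 | 0.915 |
| 0.85 | 0.768 | 0.885 | 0.573 | 0.930 |
| 0.90 | 0.818 | 0.913 | 0.702 | 0.942 |
| 0.95 | 0.878 | 0.944 | 0.852 | 0.952 |

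In patients, at AUC 0.85, the Youden point misses 147 × 0.232 ≈ 34 cases and raises 343 × 0.232 ≈ 80 false alarms. The 90% sensitivity point misses about 15 and raises 343 × 0.427 ≈ 146.

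Youden sensitivity reaches 0.90 only when d/2 = 1.2816, so AUC = Φ(2 × 1.2816/√2) = 0.965. With unequal variances (SD ratio 0.8 or 1.25) at AUC 0.80, Youden sensitivity is 0.79 or 0.67.

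**Optimism.** Simulated studies (1,000 per setting, AUC 0.70 to 0.95) chose and assessed the Youden cut-off in the same sample. Apparent minus true sensitivity at the chosen cut-off was +0.018 to +0.029, and for specificity +0.006 to +0.010.

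**Intervals.** These come from 400 runs with 200 resamples each, so coverage has Monte Carlo error of about 1 to 2.5 points. All are nominal 95% intervals for sensitivity.

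| Bootstrap | Width | Covers true Se at chosen cut-off | Covers population Youden Se |
|---|---|---|---|
| Cut-off held fixed | 0.09–0.15 | 85–90% | 54–77% |
| Cut-off re-selected in each resample | 0.13–0.36 | 89–95% | 95–98% |

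In the second row, the remaining shortfall at the chosen cut-off comes from optimism, not from width.

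**The case against.** Several stronger statements are tempting, and the protocol does not support them.

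- **That the intervals are too narrow.** Section 9 does not say that the bootstrap holds the cut-off fixed. If selection is repeated in each resample, they are not too narrow. The defect is conditional.
- **That the 95% power is wrong.** The power is conditional on a true sensitivity of 90%. Where Youden meets that condition (AUC 0.965), apparent sensitivity reached 126/147 in 95.8% of simulated studies, against 96.4% for a fixed cut-off. At lower AUC, the chance of 126/147 at the population Youden point is 0.5% (AUC 0.85), 13% (0.90) and 81% (0.95). There the planning assumption fails; the calculation does not.
- **That the study will miss its 90% target.** The 90% is a planning assumption, not an acceptance criterion, and the shortfall depends on an AUC that the protocol does not give.
- **That the primary figures will certainly be read at the Youden point.** Section 9 defines sensitivity and specificity before it mentions Youden, and its wording for ICPtcd runs parallel to that for ICPi. A common 22 mmHg cut-off, with Youden as an addition, is a possible reading. But no ICPtcd number is given, and Youden is the only rule stated.

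It is also fair to say that PPV and specificity are primary alongside NPV and sensitivity, so a balanced criterion is debatable rather than contradictory. The optimism is small next to the sampling error: with 147 cases the standard error of sensitivity is about 3.5 points at AUC 0.85. The AUC, which needs no cut-off, is also planned. These points lower the severity. They do not supply a cut-off, and they do not make Youden a rule-out criterion.

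**Conclusion.** The point holds in a limited form, and should be fixed. Section 9 leaves the ICPtcd cut-off without a number and names a criterion that targets neither exclusion nor the 90% sensitivity on which the sample size rests.

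For an AUC between 0.80 and 0.90, the Youden point lies 8 to 18 points below 90% sensitivity, and its NPV is 2.9 to 5.5 points lower than at a 90% sensitivity cut-off. The gap closes near AUC 0.965. These sizes rest on the binormal model, equal variances, 30% prevalence and an assumed AUC.

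The in-sample optimism is real but modest, and interval width is a problem only if selection stays outside the bootstrap. The 490 stands: it applies to a cut-off whose true sensitivity is 90%, which Youden does not aim for.

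**What to change.** In section 9, before any analysis:

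1. Report the primary NPV, PPV, sensitivity and specificity at one ICPtcd cut-off fixed in advance. A value above 22 mmHg, mirroring the reference, is a natural candidate. It is not thereby shown to be a rule-out point.
2. Add, as secondary, a rule-out cut-off defined by sensitivity: the highest ICPtcd value with sensitivity of at least 90%. Label Youden exploratory.
3. For every data-chosen cut-off, including the rule-out one, repeat the selection inside each of the 10,000 resamples and report optimism-corrected estimates.
4. Do not count the rule-out cut-off's apparent sensitivity as meeting the planning value. With 147 cases it is 133/147 = 90.5% by construction, while its true sensitivity falls below 90% in about half of simulated studies.

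The cost is a few sentences and a few lines of code, with no new patients or data. The price in the results is lower reported specificity at the rule-out cut-off and somewhat wider intervals.
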